## Abstract

Background: Children and adolescents should perform, according to the World Health Organization guidelines, at least 60 min of moderate-to-vigorous physical activity per-day in order to avoid the risk of metabolic and cardiovascular diseases. The school represents a fundamental setting to conduct interventions to promote physical activity (PA) and contrast sedentary behaviors. Active breaks (ABs), bouts of 10 min of PA conducted inside the classroom, seem to be a good strategy to promote PA and improve classroom behavior. The aim of this study protocol is to describe the design and the assessment of the Imola Active Breaks I-MOVE study. Methods: The I-MOVE study is a school-based intervention trial, with a quasi-experimental design, performed in a primary school. It involves one experimental-group performing the intervention, focused on ABs, and one control-group. Nine main outcomes are evaluated: PA and sedentary behaviors; health related fitness; motor control development; dietary patterns; anthropometric evaluation; sociodemographic determinants; cognitive function; time-on-task behavior and quality of life. Conclusions: Results from the I-MOVE study will help to clarify the effects of incorporating ABs in the Italian school curriculum as a new public health strategy and an innovative school model oriented to the well-being of children and teachers for the best quality of school life.

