### 2.2. School and Participant Recruitment

The study setting was a primary school in the city of Imola (70,075 inhabitants, Bologna, Northern Italy).

Invitation letters accompanied by an expression of interest form were sent to the principals of 4 schools of the city of Imola. One school expressed interest in participating in the project. After that, a member of our team visited the interested school to give a global view of the project in front of the relevant staff. Furthermore, a specific meeting with the headmaster was held to obtain the school’s agreement. Finally, we organized a presentation day to explain the project to the teachers. Ten teachers of 5 classes out of 15 agreed to be involved in the project. They attended a training course of 8 h to learn the basis of the project and the practical part of the active breaks intervention. The parents of the children received a short brochure describing the study, and an invitation to attend an informative meeting at school. The purpose of the meeting was to explain the intervention that would be carried out in the classrooms. At the end of the meeting informed consent was obtained from parents/tutors.

The I-MOVE study established the following inclusion criteria: (i) studying in 1st to 5th grade (aged 6–11 years), (ii) not having health problems or physical disability, which might limit the performance of ABs and (iii) having obtained informed consent of parents and permission for personal data processing.

Finally, 153 children were enrolled in the study (Figure 1). The mean number of children in the classes was 22. Participants were free to retire from the study at any point without giving explanations.

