### 2.5. Data Collection and Outcome Measures

During the Imola Active Breaks Study the following outcomes will be evaluated: (1) PA and sedentary behaviors; (2) health related fitness; (3) motor control development during fine and gross (locomotor) tasks; (4) dietary patterns; (5) anthropometric evaluation; (6) sociodemographic and early determinants; (7) cognitive Function; (8) time-on-task behavior and (9) quality of Life.

As shown in Table 2, all the measurements will be evaluated at baseline T0 (October 2019) and will then be assessed at mid-intervention T1 (October 2020) and at the end of the intervention T2 (June 2021) to investigate group differences and changes over time. The process evaluation will performed 6 months after the end of the intervention T3 (December 2021.)

The comparisons between T0, T1 and T2 will allow the research to determine the timing of any long-term effect of ABs and whether the effects of ABs are cumulative in time or reach a ceiling after T1 (for example, if there are cumulative effects, then performance should reveal a pattern T0 < T1 < T2; by contrast, if they reach positive effects in a few months and then stabilize, then performances at T1 and T2 should not differ).

Moreover, we planned an assessment at the mid-intervention to measure an acute effect before the daily active breaks and immediately after the 10-min bout for cognitive and time on task outcomes. During this specific mid-intervention we will monitor the amount of PA performing an active break, 10 min thrice a day, during a school day for a week. This assessment will be focused on cognitive function and time-on-task behaviors, since these could be more affected after acute exercises than chronic ones, as shown for some cognitive functions in the literature [24,25,26].

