#### 2.5.3. Motor Control Development During Fine and Gross (Locomotor) Tasks

Gross- and fine-motor competences will be assessed using an instrumented approach based on wearable inertial sensors [45,46]. The selected instrumented approach allows the quantitative analysis of motor competence characteristics (e.g., automaticity, complexity and regularity) and their longitudinal monitoring as related to age and/or motor development.

For gross-motor competence 3 inertial sensors (OPAL; APDM: Portland, OR, USA) will be attached, using elastic Velcro bands, to the lower shanks (above lateral malleolus) and lower back (at L5 level) of each child over clothes, and 3D acceleration and angular velocity is acquired from each sensor during natural and tandem gait along a 15 m straight path. Each child walks 3 times back and forth normally (for a total of 45 m) and 1 time in tandem (along the straight line, positioning the heel of the front foot in contact with the toes of the back one), prior to data collection, all participants are allowed to perform a tentative trial (10 TW strides) to ensure they understand the tandem gait instructions.

For the assessment of fine-motor competence, the 3 inertial sensors (OPAL; APDM: Portland, OR, USA) will be attached to the wrists (dorsal aspect) and lower back (at L5 level), and 3D accelerations and angular velocity will be acquired during the Placing bricks test [47]. Each child, sitting at a desk, attached 18 1 × 2 Duplo bricks one at a time onto a 6 × 12 Duplo plate using one hand, then the other for the second trial; blocks will be positioned on the side of the plate corresponding to the hand to be used, while the opposite hand was kept on the table or used to stabilize the plate according to child’s preference. For all trials data are acquired at 128 Hz sampling frequency.

Temporal parameters, variability, regularity, motor complexity, stability and rhythmicity calculated from acquired motion and represented in a graphical polar plot [46] allow one to qualitatively characterize different areas of motor control performance.

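### The section 2.5 criterion for cumulative versus ceiling effects is worded on raw performance over time, leaves out the control group, and gives no margin for a plateau

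*Protocol article*

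**What the plan says.** Section 2.5 of the protocol article schedules the outcome measures at baseline, and then has them "assessed at mid-intervention T1 (October 2020) and at the end of the intervention T2 (June 2021) to investigate group differences and changes over time". It adds that comparing the three visits "will allow the research to determine the timing of any long-term effect of ABs" and whether those effects accumulate or reach a ceiling.

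The criterion follows in brackets, introduced as an example. For accumulation: "if there are cumulative effects, then performance should reveal a pattern T0 < T1 < T2". For a ceiling: "if they reach positive effects in a few months and then stabilize, then performances at T1 and T2 should not differ". Neither half mentions the control group, a margin or a confidence interval.

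Elsewhere, the abstract describes a concurrent comparison: "It involves one experimental-group performing the intervention, focused on ABs, and one control-group". Section 2.6.1 plans a one-way ANOVA and a covariate-adjusted ANCOVA of between-group differences from baseline to follow-up, with significance at p below 0.05. It names no T1–T2 contrast and does not refer back to the cumulative-or-ceiling question. Section 2.5.3 accepts that motor measures move with age, since it speaks of "their longitudinal monitoring as related to age and/or motor development".

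**The concern.** The criterion is about the effect of active breaks but is expressed in the level of performance. On an outcome that improves with age, the two are different things. A child in a control class who grows, matures and repeats the same tests can also score higher at each visit. Three problems follow.

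- A rising raw pattern does not separate a cumulative effect from ordinary development.
- A truly stable effect does not give equal raw scores at T1 and T2, because both groups keep developing between the visits. The criterion therefore fails even in the direction in which it is worded, from hypothesis to expected pattern.
- Failing to find a T1–T2 difference is compatible with a plateau, but also with a further gain that the study is too imprecise to see.

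At stake is the timing claim: whether schools are told that benefits keep growing over two years or are complete after the first.

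**Working it through.** **Inputs from the protocol article.** T0 is October 2019, T1 October 2020 and T2 June 2021 (section 2.5, Table 2), so the steps are 12 and 8 months and the total is 20 months. Children are aged 6–11 (section 2.2). Section 2.3 gives 48 per group, a difference of 98.1 min of weekly MVPA, alpha 0.05 and power of at least 0.8. Section 2.2 gives 153 children enrolled.

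**Assumptions.** Linear maturation of 0.2–0.5 SD per year; correlation of 0.5 or 0.7 between any two visits of a child; two-sided tests (sidedness is not stated); no clustering and no dropout; either 48 per group or 76 (153/2 = 76.5; the actual split is not in the text shown).

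**Step 1, the plan's own figure.** The SD behind 48 per group is not given. Solving for it: SD = 98.1 × √(48/2) / (1.960 + 0.842) = 171.5 min, or d = 98.1/171.5 = 0.57. The figure is therefore matched only with an assumed SD. It does not bear on the criterion and is used below only to convert SD units into minutes.

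**Step 2, raw pattern with no intervention effect.** The simulation (10,000 runs per cell) used paired t-tests for T0–T1 and T1–T2 in one group. The mean gain was g over the first 12 months and g × 8/12 over the next 8. Each cell shows first the share with both steps significantly upward (read as cumulative), then the share with only the first step significantly upward and T1–T2 not significant (read as ceiling).

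| Maturation g, SD/year | n=48, r=0.5 | n=48, r=0.7 | n=76, r=0.5 | n=76, r=0.7 |
|---|---|---|---|---|
| 0.2 | 1.1% / 26.9% | 3.9% / 37.9% | 3.5% / 37.3% | 11.9% / 48.0% |
| 0.3 | 8.2% / 43.6% | 24.5% / 50.2% | 23.9% / 48.8% | 52.4% / 39.1% |
| 0.4 | 27.2% / 49.0% | 59.9% / 33.9% | 56.4% / 36.8% | 83.8% / 15.7% |
| 0.5 | 55.4% / 37.1% | 82.7% / 16.5% | 80.8% / 18.1% | 95.5% / 4.5% |

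Both readings are false here, because the effect is zero. Gains from repeat testing were not simulated; they would come on top.

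**Step 3, the same two steps net of control.** With equal maturation in both groups (0.5 SD, then 0.33 SD), the share with both net steps significantly upward was 0.0% in all four settings.

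**Step 4, a stable effect read on raw scores.** If the effect is fully reached by T1 and held, the expected raw T2 − T1 difference is g × 8/12. That is 0.2 × 8/12 = 0.13 SD up to 0.5 × 8/12 = 0.33 SD, not zero.

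**Step 5, the plateau reading, even net of control.** The standard error of the between-group difference in T1–T2 change is √(2(1 − r)) × √(2/n) in SD units. The chance of missing a true further net gain δ is 1 − Φ(δ/SE − 1.96). Half the planned difference is 49.05 min, or 49.05/171.5 = 0.286 SD.

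| | n=48, r=0.5 | n=48, r=0.7 | n=76, r=0.5 | n=76, r=0.7 |
|---|---|---|---|---|
| Missed, δ = 0.2 SD | 83.6% | 75.6% | 76.6% | 64.4% |
| Missed, δ = 0.286 SD | 71.2% | 56.0% | 57.8% | 37.6% |
| 95% CI half-width, SD | 0.40 | 0.31 | 0.32 | 0.25 |
| The same in min/week of MVPA | 68.6 | 53.1 | 54.5 | 42.2 |

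An interval that reaches 42–69 min either side of its estimate cannot, merely by including zero, exclude a sizeable further gain. Clustering in classes would widen it.

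**The case against.** The strongest reply is that this is an illustration and not an analysis rule. It is bracketed, offered as an example, and argues from hypothesis to expected pattern. The sentence concerns effects of active breaks, which already implies a comparison. The visits are said to serve group differences, a control group exists, and section 2.6.1 plans a between-group ANCOVA. Exact contrasts and margins are also commonly left to an analysis plan.

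Much of this stands, and it limits what may be concluded. A reader might infer any of the following, which the document does not support:

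- That the study will declare cumulative benefit whether or not active breaks work. The planned between-group analysis counts against this.
- That season or the summer break explains the whole rising pattern. T0 and T1 are both in October, so an October–June contrast can affect only T1 versus T2.
- That the plan treats no difference as proof of a plateau. It says only what should be seen if effects stabilise.
- That the acute assessment ("we planned an assessment at the mid-intervention to measure an acute effect before the daily active breaks and immediately after the 10-min bout") is uncontrolled. The text does not say how it will be analysed or that control classes are excluded.
- That speaking of effects within a few months is a serious fault. An effect reached early and held is compatible with equal effects at T1 and T2, although a visit at 12 months cannot date it.

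What the reply does not remove is that section 2.5 promises to determine the timing and gives raw performance as its only criterion, while section 2.6.1 supplies no T1–T2 contrast for the question. The stable-effect half is wrong for age-dependent outcomes even as an illustration. The point is thus about a criterion that is stated and badly fixed, not about detail left out.

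**Conclusion.** The concern holds in limited form. As worded, the criterion cannot separate cumulative from ceiling effects on outcomes that change with age. With no intervention effect, the raw cumulative pattern appears in about 1–12% of trials at 0.2 SD per year and 55–96% at 0.5, against about 0% net of control. A true further net gain of 0.2–0.29 SD goes undetected in about 38–84% of trials, before clustering.

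The maturation rates and correlations are assumptions, since the document gives none; the wide range reflects that, and no single error rate should be quoted. The near-zero net figure needs equal maturation in both groups. This is not guaranteed, because classes entered through their teachers' agreement and not by randomisation. The argument is made for fitness, motor control and digit span; it is not shown for the accelerometer outcome used for sample size, whose drift with age the document does not state.

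This is a should-fix on a secondary timing question. It does not undermine the planned main comparison of the groups.

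**What to change.** Restate the criterion in section 2.5 on D(t), the between-group difference in baseline-adjusted change at visit t, estimated with class accounted for and with outcomes scored so that higher is better (the Harre circuit and the shuttle run are timed). Report D(T1) first, since without an effect at T1 there is nothing to accumulate or to level off. Then:

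- cumulative, if the confidence interval for D(T2) − D(T1) lies above 0;
- plateau, only if that interval lies within a pre-stated margin around 0;
- otherwise inconclusive.

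The rule cannot be applied to time-on-task behaviour, which has no T0 assessment in Table 2. Say also that the T1–T2 step compares October with June. The contrast with control removes that shift only if it is the same in both groups.

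The cost is more than rewording. A group-by-time contrast must be added to the ANOVA/ANCOVA in section 2.6.1, and a margin must be set for each outcome on which a timing claim will be made. Given the half-widths above, many timing results will be inconclusive. No new data are needed.

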#### 2.5.1. PA and Sedentary Behavior

The time spent on physical activity and sedentary behavior will be calculated through actigraph accelerometers (ActiLife6 wGT3X-BT). The actigraph accelerometer models GT3X (ActiGraph LCC: Pensacole, FL, USA) is used to monitor objectively the daily PA and sedentary behavior over seven consecutive days. We examined the accelerometer data through ActiLife 6.13.3 software (ActiGraph LCC: Pensacole, FL, USA).

The epoch length will analyze to 10 s to allow a more detailed estimate of PA intensity [27]. The screening and data processing procedures to evaluate time spent in sedentary, total PA and PA at different intensities are consistent with previous studies on children and adolescents [28,29,30]. The children will wear the accelerometers over a seven-day period (five weekdays and two weekend days), only to be removed when bathing, swimming and showering. Accelerometers are attached around the waist with an elastic belt, in line with the existing literature [31].

We will analyze the accelerometer’s data only when children complying with some specific inclusion criteria: having worn the accelerometer on at least 3 weekdays and 1 weekend day, and for at least 10 h every day (including sleeping hours). Minutes spent in physical activity (light, moderate and vigorous) per day will be calculated using the Evenson cut points [32].

PA will also be evaluated with the physical activity questionnaire for children (PAQ-/C).

The PAQ-C is a self-administered, 7-day recall questionnaire, with 9 items scored on a five-point scale. This instrument provides a final composite activity score, by taking the mean of the 9 items. This questionnaire has been shown to be valid and reliable [33].

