### 2.3. Sample Size

Sample size was estimated considering the actigraph accelerometers as a primary outcome measure of the study. Sample size calculations were based on the pilot and feasibility study [21], which detected a mean difference of 98.1 min in weekly total MVPA, measured using the accelerometer, between the intervention group and control group.

Considering an alpha error of 0.05 and a power of at least 0.8, the minimum size of the sample was estimated as 48 participants per group, for a total of 96 participants, without considering the nested data structure. Power analysis was carried out with Clinicalc.com.

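### The accelerometer wear rule counts sleep toward the 10-hour minimum, so a day with little or no waking data can enter the primary MVPA measure

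*Protocol article*

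**What the plan says.** Section 2.3 (Sample Size) makes the accelerometer the primary measure: "Sample size was estimated considering the actigraph accelerometers as a primary outcome measure of the study". The quantity used for sizing is a "mean difference of 98.1 min in weekly total MVPA" taken from the pilot study, which leads to 48 children per group.

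Section 2.5.1 (PA and Sedentary Behavior) sets the wear instruction and the validity rule:

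- The device is worn for seven days, "only to be removed when bathing, swimming and showering". It is therefore kept on at night.
- A child's data are analysed after "having worn the accelerometer on at least 3 weekdays and 1 weekend day", and each such day counts if the device was worn "for at least 10 h every day (including sleeping hours".
- Minutes of light, moderate and vigorous activity "per day will be calculated using the Evenson cut points".
- For processing in general, the article refers to other work: "The screening and data processing procedures to evaluate time spent in sedentary, total PA and PA at different intensities are consistent with previous studies".

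The section sets no minimum of waking wear and states no step that identifies or removes sleep.

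**The concern.** A wear-time threshold is there to ensure that enough of the active day was observed for the day's activity minutes to mean something. MVPA happens only while a child is awake. If the night counts toward the threshold, most or all of the 10 h can be met in bed, and the rule no longer screens out days on which the device was left off during waking hours.

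Such a day is not treated as missing. It enters the data as an observed day with MVPA near zero. This bears directly on the contrast of interest: Section 2.4 places the active breaks in the classroom on weekdays, so a weekday with no school-time wear cannot show any effect of them. If these days are equally common in both groups, they dilute the difference. If they are more common in one group, they bias it. Aim 1 (total-day and school-day activity, and sedentary time) depends on this measure.

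**Working it through.** **Inputs from the article.** Threshold 10 h per day with sleep counted, and 3 weekdays plus 1 weekend day (Section 2.5.1). Difference 98.1 min of weekly MVPA, alpha 0.05, power at least 0.80, 48 per group, nesting ignored (Section 2.3).

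**Assumptions, not in the article.** Sleep of 8 to 11 h; true MVPA of 60 min per day spread evenly over waking time; a two-sided test; a range of frequencies for sleep-only days.

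**Step 1: the plan's sample size.** The article gives no SD, so 48 per group cannot be reproduced independently. Solving the normal-approximation formula backwards:

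SD = 98.1 / [(1.960 + 0.842) × √(2/48)] = 171.5 min.

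A one-sided test would imply 193.3 min. The 171.5 min is used below only to give a scale; the sample size itself is not disputed here.

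**Step 2: waking wear needed for a valid day.** As written, minimum waking wear = max(0, 10 − sleep). Recorded MVPA = 60 × (waking wear) / (24 − sleep).

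| Assumed sleep (h) | Waking hours | Minimum waking wear, rule as written (h) | MVPA recorded of 60 min | Share of waking time if 10 h must be waking | MVPA recorded of 60 min |
|---|---|---|---|---|---|
| 8 | 16 | 2 | 7.5 | 10/16 = 63% | 37.5 |
| 9 | 15 | 1 | 4.0 | 10/15 = 67% | 40.0 |
| 10 | 14 | 0 | 0 | 10/14 = 71% | 42.9 |
| 11 | 13 | 0 | 0 | 10/13 = 77% | 46.2 |

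A just-valid day therefore covers 0% to 12.5% of waking time under the present rule, against 63% to 77% under a waking-wear rule.

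**Step 3: does the definition of a day prevent this?** The article does not say when a day begins. Suppose it runs from midnight to midnight. Wear at 00:00–07:00 gives 7 h and wear at 21:00–24:00 gives 3 h, together 10 h. The day is valid with no daytime data.

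**Step 4: illustration of dilution.** Let a fraction f of analysed days in both groups be sleep-only and record no MVPA. The expected difference becomes 98.1 × (1 − f). With the SD held at 171.5 min and 48 per group, the standard error is 171.5 × √(2/48) = 35.0 min, and power = Φ(difference / 35.0 − 1.960).

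| f | Difference (min/week) | Power |
|---|---|---|
| 0 | 98.1 | 0.80 |
| 5% | 93.2 | 0.76 |
| 10% | 88.3 | 0.71 |
| 20% | 78.5 | 0.61 |

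This supposes that sleep-only days fall evenly on the days that carry the group difference, and that they leave the SD unchanged.

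**The case against.** The strongest reply is that the wear instruction already covers the problem. A child who takes the device off only for water activities has nearly complete waking wear, and counting sleep changes nothing in that child's MVPA. The failure needs a child who wears the device in bed and leaves it off by day, against instruction. With midnight-to-midnight days, morning wear alone (7 h in the example above) fails the threshold, and the device must go back on for about 3 more hours. The article gives no compliance data, so the frequency may be low. All of this stands, and it limits the severity. It does not rescue the rule, because a validity criterion exists to catch days on which the instruction was not followed.

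Three stronger readings are tempting but unsupported:

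- *Sleep is scored as sedentary time.* The article does not say so. Its sentence on cut points covers light, moderate and vigorous activity, and sedentary processing is deferred to cited studies that may contain a sleep-removal step. Only the conditional statement holds: if no such step is applied, sleep would be counted in sedentary time.
- *Weekly MVPA is distorted by summing or averaging over as few as four days.* The article gives minutes per day and does not specify how days are combined. The weekly figure describes what the pilot found. The method of aggregation can be left to a fuller plan.
- *The group comparison is biased by a known amount.* For example, with 14 waking hours and one of them worn, a day loses 60 × (1 − 1/14) = 55.7 min. A 10-point difference between groups in the frequency of such days would then shift the mean by 5.6 min per day, or 40% of 98.1/7 = 14.0 min. The arithmetic is right, but nothing in the article supports a 10-point difference or says which group it would favour.

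**Conclusion.** The rule is wrong as written, on the measure that the article calls primary. Because sleep counts toward the 10 h, a day can qualify with 0 to 2 waking hours (for 8 to 11 h of assumed sleep) and be analysed as a near-zero day. That such days can enter follows from the stated rule; that they often do is not shown.

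The effect on the trial depends on their unknown frequency. If they are equally common in both groups, at 5% to 20% of analysed days, power falls from 0.80 to between about 0.76 and 0.61, on an SD inferred from the sample size and held fixed. Unequal frequency would bias the comparison, by an amount and in a direction that the article gives no means to estimate.

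This is a should-fix point: the defect is clear, but its practical size is not established, and MVPA in compliant children is unaffected.

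**What to change.** Change the validity rule in Section 2.5.1 to at least 10 h of *waking* wear per valid day. State that sleep is identified and excluded before wear time and sedentary minutes are computed, and how. If the cited procedures already do this, say so and correct the parenthesis, because removing sleep afterwards does not repair a day that was admitted on the strength of sleep.

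The cost is one changed sentence and reprocessing of recordings already made. The real downside is data loss: there will be somewhat fewer valid days, and some children may no longer meet the criterion of 3 weekdays plus 1 weekend day. The number of days and children lost in each group should be reported. The article gives no basis for estimating that loss in advance.
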